### Follow-up evaluation

Physical activities and other leisure time activities will be measured during the 6 months follow-up via telephone interviews. This is to monitor changes among participants in activities that can enhance performance on tests, apart from Tai Chi and routine exercise. The self-completed quality of life questionnaire will be mailed to participants after 2 months from randomization. All baseline measurements will be repeated at 6-month follow-up. Researchers performing all measurements will be blinded to group allocation and participants will be required not to reveal to researchers which group they were in (Table 1).

**Table 1 Tab1:** **Schedule for data collection; outcome measures per visits**

**Measures**	**Baseline (0-week) (T0)**	**End of treatment (8-week) (T1)**	**The first follow-up (24-week) (T2)**
Demographic characteristics	×		
PD history	×		
BBS	×	×	×
TUG	×	×	×
6WMT	×	×	×
UPDRS-III	×	×	×
PDQ-39	×	×	×
Adverse experiences^a^		×	×
Combined medication^b^		×	×

^a^Adverse experiences: any adverse experiences at any visit during treatment sessions and 24 weeks will be monitored. The research team will review all trial protocols, monitor patient safety and investigate any adverse events. ^b^Patients will be asked whether they have used other medication during the treatment. If they have used concomitant medications then the type and dose of medication taken by them will also be recorded in detail.

*Abbreviations:* 6MWT, Six-Minute Walk Test; BBS, Berg Balance Scale; PD, Parkinson’s disease; PDQ-39, Parkinson’s Disease Questionnaire-39; TUG, Timed Up and Go Test; UPDRS-III, Unified Parkinson’s Disease Rating Scale Motor Section.

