## Methods and Design

### Trial design

A single-blind (assessors), parallel randomized controlled trial will be conducted to compare Tai Chi with routine exercise (allocation ratio 1:1). The study period is 8 months including a 2-month supervised intervention and a 6-month follow-up with the primary outcome measured at baseline, 2 and 8 months. The primary site for conduct of the study, including all study visits and Tai Chi interventions will be conducted at the Affiliated Hospital of Jining Medical University, Jining, Shandong, China. Routine exercise will be conducted in a home-based environment.

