### Intervention

#### Tai Chi

The intervention will be composed of 1-hour group Tai Chi classes customized for patients with PD, and held 3 times weekly for 2 months. The program will include traditional warm-up exercises, followed by 6 simplified Tai Chi movements taught by 2 certified and experienced instructors (average experience of 20 years). Warm-up exercises (15 minutes) will include weight-shifting, arm-swinging, gentle stretches of the neck, shoulders, spine, arms, legs, visualization techniques, and traditional breathing methods (that is whole-body breathing). These exercises will help release tension in the physical body, incorporate mindfulness and imagery into movement, increase awareness of breathing, and promote overall relaxation of body and mind. The core Tai Chi movements (45 minutes) will be adapted from the Yang Short-form style of Master Cheng Man-ching [16], and performed repetitively. The six movements are as follows: (1) wave hands like clouds; (2) part the wild horse’s mane on both sides; (3) step up and thrust downward; (4) strike to ears with both fists; (5) repulse monkey; (6) grasp sparrow’s tail. These movements were selected because they are easy to comprehend and emphasize repeated bilateral stepping with body-weight transfer that is helpful to retain postural stability for PD patients. Chairs will be provided for resting, and patients will be allowed to progress at their own comfort and pace. After 2 months of training, the Tai Chi group will be provided with a 30-minute instructional videotape that outlines the exercises presented in class. Patients will be required to continue to practice at home at least three times per week. Class attendance will be monitored, and adherence to practice will be tracked via self-report logs, which obtain the weekly frequency and duration of home Tai Chi practice.

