### Routine exercise

Subjects allocated to the control group will not receive any specific training from the study schedule. They will be requested to keep their original habit of routine exercise (except Tai Chi) such as walking, dancing, cycling, and so on, and they will also be requested to practice for 1 hour at a time, 3 times a week in the training period as well as the follow-up. The follow-up training for both groups will be monitored by phone call.

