### Assessment procedures

Data from patients and caregivers will be collected at baseline (T0), 2 months (T1) and 8 months (T2) by 2 research assistants. Another 3 selected and trained occupational therapists will score the BBS, TUG, 6MWT, UPDRS-III and PDQ-39 in an activity that is video- recorded by the assessor. The data collected from the assistants and therapists will be entered in a dedicated computer and kept in a secure and lock-protected location. All assessors and scorers are blinded for group allocation and each participant will be followed up by the same assessor. To test the quality of home-based routine exercise, patients and caregivers will fill in all self-report records. Observational tests or measures that follow a semi-structured interview format will be conducted in the patient’s home environment by the assessor. Considering possible response fluctuations in PD, measures will be administered 1 hour after medication intake (the ‘ON’ phase). For budgetary reasons, the 6-month follow-up training will be monitored by phone call and the data for assessment will be finally collected by the same assessor.

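### Table 1, footnote a, ties adverse-experience monitoring to treatment sessions that only the Tai Chi arm has between T0 and T1, so a simple count by arm for the training period would be biased

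*Protocol article*

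**What the plan says.** All references are to the protocol article.

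- **Table 1** ("Schedule for data collection; outcome measures per visits") marks adverse experiences at T1 and T2, not split by arm. Footnote a adds that "any adverse experiences at any visit during treatment sessions and 24 weeks will be monitored".
- **Tai Chi** describes instructor-led group classes "held 3 times weekly for 2 months". It adds: "Class attendance will be monitored, and adherence to practice will be tracked via self-report logs". Trial design places these classes at the hospital.
- **Routine exercise** states: "Subjects allocated to the control group will not receive any specific training from the study schedule". Trial design adds: "Routine exercise will be conducted in a home-based environment".
- **Routine exercise** also says: "The follow-up training for both groups will be monitored by phone call". Assessment procedures and Follow-up evaluation likewise mention telephone contact only for the 6 months after training.
- **Assessment procedures** says that "patients and caregivers will fill in all self-report records", and gives as the purpose a check on the quality of the home exercise.
- **Ethics** offers a 24-hour clinic contact, which the patient initiates when symptoms deteriorate unexpectedly.

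**The concern.** The footnote attaches safety monitoring to an occasion that one arm has and the other does not. Suppose a participant falls or strains a muscle in week 2. In the Tai Chi arm, the next class with two instructors present is at most a few days away. In the control arm, the first described occasion to report it is T1, about 6 weeks later, when it may be forgotten or judged not worth mentioning. The 24-hour line does not even this out, since a strain, or a fall without worsening of symptoms, need not prompt a call.

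The article says that the trial will inform whether Chinese patients with Parkinson's disease should be advised to practise Tai Chi, and it enrols up to Hoehn and Yahr stage 4. Even a purely descriptive table of events by arm would feed into that advice. If one column was collected more closely than the other, equal true rates would look unequal, or a true excess among controls could be hidden.

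**Working it through.** The plan states no figure to reproduce here. The check has two parts: a count of occasions, and the direction of the bias.

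**1. Occasions at which an adverse experience could come to the study's notice**

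| Period | Tai Chi | Control |
|---|---|---|
| T0 to T1, classes | 3 per week × 8 weeks = 24 | 0 |
| T1 visit | 1 | 1 |
| Total up to T1 | 25 | 1 |
| After T1 | follow-up calls and T2 | follow-up calls and T2 |

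The inputs are the class frequency and duration (Tai Chi), the absence of study training for controls (Routine exercise), the T1 and T2 entries (Table 1) and the calls to both groups (Routine exercise). Table 1 puts T1 at 8 weeks. Counting two calendar months as 8.7 weeks gives 3 × 8.7 ≈ 26 classes, so 27 against 1. These are opportunities for an event to be noticed. The article does not say that each class includes an adverse-event enquiry.

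**2. Direction of the bias**

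Let the true event rate be the same in both arms, λ. Let the share of events recorded be c_T in the Tai Chi arm and c_C in the control arm.

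Apparent rate ratio = (λ × c_T) / (λ × c_C) = c_T / c_C.

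The true rate cancels, so the apparent ratio reflects capture alone. It exceeds 1 whenever classes raise capture in the Tai Chi arm. The article gives no capture shares. The values below are **assumptions**, used only to show how the ratio behaves:

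- c_T = 0.90, c_C = 0.70: 0.90 / 0.70 = 1.29
- c_T = 0.90, c_C = 0.50: 0.90 / 0.50 = 1.80
- c_T = 0.90, c_C = 0.30: 0.90 / 0.30 = 3.00

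The range restates what was assumed and is not an estimate for this trial. If classes added nothing to capture, the ratio would be 1.

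If instead both arms are counted only from the same questions at T1, with equal recall c_C in each, the ratio is c_C / c_C = 1. There is recall loss, but it is the same in both arms.

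**The case against.** Several points on the other side carry weight.

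- **The common schedule exists.** Table 1 marks adverse experiences at T1 and T2 for both arms, and follow-up contact is described alike for both. A reader might infer that the two arms' safety results cannot be compared at all. The documents do not support that: events elicited in the same way at T1 and T2 could be compared fairly, and only the 2-month training window is exposed.
- **The wording is loose.** The article calls both arms treatment groups, labels T1 as the end of treatment for everyone, and speaks in the Abstract of supervised programs without distinguishing arms. The footnote may have been meant to cover the treatment period. But Trial design and Routine exercise contradict the Abstract's supervision for controls. Even on the wider reading, no control visit between T0 and T1 is described at which monitoring could occur.
- **Classes are not said to record adverse events.** Only attendance is said to be monitored. A reader might take 25 against 1 as counts of enquiries, or the assumed ratios as a forecast. Neither is supported.
- **No between-arm safety test is stated.** The efficacy section does not mention one, and the hypothesis concerns symptoms, gait, balance and quality of life. This limits the consequence to descriptive safety reporting.
- **An article condenses.** Interim calls or event forms may be in the full protocol, and Assessment procedures mentions home-based assessment without stating when. Their absence here is therefore not the complaint. The complaint is that the rule the article does state applies unequally to the two arms.

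**Conclusion.** The point holds in a limited form. Read literally, footnote a gives closer ascertainment in the Tai Chi arm between T0 and T1. A simple comparison of adverse-event counts that includes this period would be biased, most likely against Tai Chi. The size is unknown.

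The conclusion rests on three conditions: that the footnote is followed as worded, that attending classes makes an event more likely to be recorded, and that no control contact before T1 exists beyond those described. The follow-up period and the efficacy analysis are not affected. It is a defect in data collection that a change of wording can repair.

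**What to change.** Reword footnote a so that adverse experiences, including falls, are elicited with the same fixed questions in both arms at T1, in the follow-up calls and at T2. State that any between-arm safety comparison uses this common source only. Tabulate events noted in Tai Chi classes separately, as safety information on that arm.

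If weekly capture between T0 and T1 is wanted, give the same short log to both arms from T0. The logs already described cannot be assumed to serve. The Tai Chi log records home practice, which is described only for the time after the classes end, and the stated purpose of the self-report records in Assessment procedures is to check the quality of home-based routine exercise.

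The contacts at T1, by phone and at T2 are already planned, so the core change costs one set of questions and a revised footnote. The downsides are slightly more form-filling, some recall loss in both arms, and class-observed events that sit outside the comparison. An optional log adds a new form for participants to complete.

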### Sample size

The sample size was calculated based on a pilot study (not published), including 10 patients with PD (1 to 4 on the Hoehn and Yahr scale) who participated in the Tai Chi exercise. To detect a difference of 4.0 in BBS and assume a standard deviation of 7.2, the sample size of 116 was required at 80% power and 2-sided significance alpha level of 0.05. According to the previous study, the significant difference between Tai Chi and stretching training was reported in TUG of patients with PD based on a sample size of 65 in each group [16]. Therefore, the optimal simple size, in anticipation of a 20% drop-out, would be 71 per group (total 142).

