**Methods/Design:**

A single-blind, parallel randomized controlled trial will be conducted. One hundred and forty-two patients with PD will be randomly assigned to a Tai Chi group (n = 71) or routine exercise group (n = 71). Subjects will participate in supervised study programs 3 times per week for 2 months and will be followed for an additional 6 months after formal training stops. The primary outcome measures include Berg Balance Scale, Timed Up and Go Test and Six-Minute Walk Test, which are known to be valid and reliable clinical instruments. The Unified Parkinson’s Disease Rating Scale Motor Section and Parkinson’s Disease Questionnaire-39 will be used as the secondary outcome measure. All outcomes will be measured at baseline, 2 and 8 months. The sample for this trial (N = 142) will provide relevant information to detect the improvement of balance, gait and quality of life in either of the 2 exercise groups.

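### The stated BBS inputs need 102 to 104 patients for 80% power, not 116; the error is conservative and N = 142 can stand

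*Protocol article*

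**What the plan says.** The Sample size section bases the calculation on an unpublished pilot of 10 patients and gives all the usual inputs: "To detect a difference of 4.0 in BBS and assume a standard deviation of 7.2, the sample size of 116 was required at 80% power", with "80% power and 2-sided significance alpha level of 0.05". It does not name the test or formula, and it does not say whether the SD of 7.2 belongs to the BBS score or to its change from baseline.

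The next sentence cites an earlier comparison of Tai Chi with stretching, in which a significant difference "was reported in TUG of patients with PD based on a sample size of 65 in each group". The paragraph then concludes, with a connecting *therefore*, that the best size, "in anticipation of a 20% drop-out, would be 71 per group (total 142").

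Trial design gives the allocation ratio as 1:1. Efficacy analysis of outcome measures sets the primary analysis as an ANCOVA of BBS change adjusted for baseline BBS. It counts patients who withdraw as unchanged from baseline from then on.

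**The concern.** A sample-size statement is meant to be reproducible: difference, SD, alpha, power and allocation together fix N. Here all five are printed, and the N beside them does not follow. A reader who checks the figure cannot tell whether the trial was planned at a higher power than stated, with a larger SD or a smaller difference than stated, or with a margin that is not mentioned.

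The steps from 116 to 142 do not close exactly either, and a study with 65 per group stands between the calculation and the conclusion without being used in a visible way. What is at stake is the credibility of the stated power and drop-out allowance, against which the finished trial will be judged. The number of patients enrolled is not at stake.

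**Working it through.** **Inputs.** From Sample size: difference 4.0, SD 7.2, power 80%, two-sided alpha 0.05, required size 116, drop-out 20%, planned size 142. From Trial design: allocation 1:1. The 116 is read as a total, 58 per group.

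**Step 1: try to reproduce 116.** For two means with equal groups,

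n per group = 2 × (SD/difference)² × (z for alpha + z for power)²
= 2 × (7.2/4.0)² × (1.960 + 0.842)² = 50.9, so 51 per group and 102 in total.

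The t-test (noncentral t) gives 51.8, so 52 per group and 104 in total. The stated 116 is 12 to 14 patients more.

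**Step 2: what 116 corresponds to.**

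| Patients per group | Power, t-test | Power, normal |
|---|---|---|
| 52 | 80.1% | 80.9% |
| 56 | 83.0% | 83.6% |
| 57 | 83.7% | 84.3% |
| 58 | 84.3% | 84.9% |
| 71 | 90.8% | 91.2% |

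So 58 per group is close to the size for 85% power (59 by the normal approximation). To need 58 per group at exactly 80% power, the SD would have to be about 7.6 (t) or 7.7 (normal) with the difference at 4.0. Alternatively, the difference would have to be about 3.8 (t) or 3.7 (normal) with the SD at 7.2.

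**Step 3: other readings.**
- One-sided test: 41 per group.
- Two-sided alpha 0.025: 62 to 63 per group.
- Alpha 0.05/3, for three primary measures: 68 to 70 per group.
- Paired or one-sample design: 28 patients.
- 116 taken as the size of each group: about 98.8% power.
- 2:1 allocation: 117 in total, but the protocol states 1:1.

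No reading consistent with the protocol gives 58 per group.

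**Step 4: from 116 to 142.** 142 × 0.8 = 113.6, so about 113 patients remain, not 116. Dividing by the retained fraction gives 116/0.8 = 145, or 73 per group (146). Multiplying instead gives 116 × 1.2 = 139.2, so 140. Neither is 142. The loss that takes 142 to 116 is 1 − 116/142 = 18.3%.

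**Step 5: the 65 per group.** 2 × 65 = 130, which is neither 116 nor 142. Going from 71 to 65 is a loss of 1 − 65/71 = 8.5%, not 20%.

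**Step 6: what the stated inputs need after drop-out.** 51/0.8 = 63.75, so 64 per group (128). 52/0.8 = 65 per group (130). The planned 142 exceeds both by 12 to 14.

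**The case against.** The strongest reply is that nothing depends on the slip. The stated inputs need 128 to 130 randomised, 142 are planned, and completer power is 83-84% against the 80% promised. The section names no method, so the 116 may hold a margin of about 14% (58/50.9) that the article leaves out. This stands as a reason for low severity. It does not rescue the sentence, which says that 116 is what 80% power requires.

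The reply also stands on the drop-out step. The gap between 142 and 145 is about 2%, and 113 completers are still more than the 102 to 104 that the inputs need.

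A reader might infer more than the document supports:

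- **That 65 per group was a target the trial misses.** Inflating 65 for 20% loss would give 65/0.8 = 81.25, so 82 per group. But the text gives 65 only as the size of an earlier study. The fair criticism is that its role is unexplained.
- **That the abstract claims power for gait and quality of life.** It says the sample will give information "to detect the improvement of balance, gait and quality of life in either of the 2 exercise groups". That is loose wording, but it attaches no power figure to those outcomes. The body of the article states a between-group hypothesis and sizes the trial on BBS.
- **That power under the planned analysis is below 80%.** If 4.0 is the effect in completers and 20% of each arm is set to no change, the effect becomes 0.8 × 4.0 = 3.2. With 71 per group, power is then about 75% if the SD stays at 7.2. It is 78% to 83% if the SD shrinks with the added zeros (6.92 down to 6.54, for assumed control gains of 4 down to 0 points). The protocol states neither the completer reading of 4.0 nor any control gain. These figures also leave out any gain from baseline adjustment, and the second range includes 80%. They show dependence on assumptions, not a shortfall.

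**Conclusion.** The stated requirement is wrong as written. With difference 4.0, SD 7.2, two-sided alpha 0.05, 80% power and equal groups, the size is 102 (normal) or 104 (t), not 116, and 116 gives about 84% power. The overstatement is 12 to 14 patients. This rests on a two-sample comparison of means with 116 as a total. If 7.2 is an unadjusted SD, the planned ANCOVA would need no more patients than this. Which figure is misstated cannot be settled from the article.

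The drop-out step (about 113 left, not 116) and the unexplained 65 per group are minor notes on the same paragraph. This is a minor reporting correction: it does not show an underpowered trial and gives no reason to change enrolment.

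**What to change.** Keep N = 142 and correct the paragraph in one of two ways.

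1. If the SD, difference or power was misprinted, print the true value and confirm that it gives 116.
2. Otherwise restate along these lines: *A between-group BBS difference of 4.0 with SD 7.2 needs 52 patients per group (104 in total) for 80% power at a two-sided alpha of 0.05. With 142 randomised and 20% drop-out, about 113 are evaluable, which gives about 83-84% power by a two-sample t-test.*

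In either case:
- name the method, and say whether 7.2 is the SD of the score or of the change;
- show the drop-out step as a division by 0.8;
- remove the 65-per-group study as a basis for 71, or say what it contributes;
- say that the power figure is a completer calculation, because the primary analysis sets withdrawals to no change. If power under that rule is also quoted, state the assumed control gain, SD and baseline correlation with it.

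The cost is a few sentences of wording. Enrolment, visits and analysis stay as they are.

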### Ethics

The study has been approved by the Medical Ethics Committee of Affiliated Hospital of Jining Medical University (number 20140327). The investigator will explain the benefits and risks of participation in the study to each subject and will provide an informed consent form approved by the Ethics Committee. Only patients who sign the form will be included in the study. Results will be published anonymously. If there is an unexpected worsening of motor or neuropsychiatric symptoms, patients can immediately contact our clinic 24 hours a day and will be immediately referred to a neurologist specializing in PD.

## Discussion

It is important to realize that the role of exercise should not be considered a cure for the disorder but rather a strategy for maintaining as much normal function as possible. Assessing balance, gait, aerobic fitness, flexibility, agility, coordination, strength and quality of life has become a challenge for fitness professionals working with older adults and those with PD. Currently, there are no established exercise guidelines to appropriately evaluate these factors.

This trial will be the first to compare the effect of Tai Chi training and routine exercise in people with PD in mainland China. Presently, Tai Chi is frequently used as a daily health cultivation exercise in the Chinese population, especially for the older people; although it has been used to test its effectiveness in some diseases such as insomnia, low back pain and even stress, it is, however, not clear whether Tai Chi should be advocated in Chinese patients with PD. Recently, the beneficial role of Tai Chi on PD has been reported in some countries; however, most of them just focus on the recovery of motor function and there is a lack of reliable evidence of follow-up effect for Tai Chi. The best type of exercise to help the PD population likely depends on which best addresses the efficiency of treatment. This trial will reveal the effect of Tai Chi, not only on focusing on balance and gait performance, but also on health-related quality of life, and for a follow-up period of 6 months. This data will assist in investigating the impact of Tai Chi for people with PD who are still mobile and living in their own homes. There are also some limitations in our trial. This is a single-center study and the number of participants included in our study is not large (a total of 142 patients was planned to be recruited). Moreover, the lack of patient blinding may increase bias.

Tai Chi is a traditional Chinese mind-body exercise, continuous in sequence, deep in breath and slow and smooth from one movement to another. It is moderate in exercise intensity. A recent review has reported that moderate intensity exercise may be a reasonable choice for people with PD [31]. Findings from this study will provide insights for Chinese practitioners into the effects of Tai Chi in people with PD. The information gained from this project has the potential to influence the clinical decisions of Chinese doctors, and will provide clear evidence as to whether Tai Chi should be advocated in people with PD. The results of the completed study will be reported according to the Consolidation of Standards for Reporting Trials guidelines [32].

